### Treatments

There will be no protocol mandated treatments or interventions outside of routine post-transplant monitoring as annotated in Table 1. Any interventions, alterations, and/or reinstitution of immunosuppression will be at the sole discretion of the treating physician. Reinstitution of transplant immunosuppression in subjects who successfully achieved functional immune tolerance as defined in the parent study should only be for cause (e.g., biopsy-proven acute rejection). Should immunosuppression be reinstituted, the subject should continue in the study and follow the schedule of assessment given in Table 1. The only non-SOC monitoring will be assessment of mixed chimerism on an annual basis in subjects who maintain the mixed donor chimerism (> 5%). As this is a strictly observational study, there is no rationale for early termination rules or criteria.

### Discontinuation and withdrawal

Withdrawal of individual subject(s)

A subject is free to withdraw from the study at any time without giving reason for doing so and without penalty or prejudice. The investigator is also free to terminate a subject’s involvement in the study at any time if a subject’s clinical condition warrants it.

Subjects who withdraw all consent for further participation in the study will be withdrawn from all follow-up assessments and will only be followed for mortality through public records. Subjects should have an end of the study visit completed shown in Table 1 at the time of their discontinuation.(2)Discontinuation of the site

If an investigator intends to discontinue participation in the study, the investigator must.immediately inform the sponsor. The sponsor will provide written notice for sitetermination.(3)Discontinuation of the study

The sponsor may terminate this study prematurely, either in its entirety or at any study site, for reasonable cause provided that written notice is submitted in advance of the intended termination. If the sponsor terminates the study for noncompliance reasons, the sponsor will immediately notify the investigators and subsequently provide written instructions for study termination.

### Assessment of safety

Safety will be assessed using incidence of serious adverse effects (SAEs) and adverse effects (AEs) leading to study withdrawal (SAEs and AEs defined below); review of laboratory data, including hematology, biochemistry (comprehensive metabolic profile), and urinalysis; hospitalization rates; and vital signs yearly during the study follow-up period.

The coding dictionary for this study will be the Medical Dictionary for Regulatory Activities (MedDRA). It will be used to summarize AEs by system organ class and/or preferred term. The version of MedDRA to be used will be determined prior to final database lock.

### Safety parameters

Vital signs

All recipients will have vital signs (systolic and diastolic blood pressure, pulse, respiratory rate, and temperature) collected at all yearly study visits. After the subject has been sitting for 5 min, with back supported and both feet placed on the floor, systolic and diastolic blood pressure will be measured with an appropriately sized cuff and calibrated machine.(b)Physical examination

A complete physical examination will be performed on all recipient subjects as part of the annual safety evaluation study visits. Significant findings that are present prior to signing the Informed Consent Form must be included in the Medical History screen on the subject’s case report form (CRF). The investigator or a qualified designee will conduct the exams, determine findings, and assess any abnormalities as to clinical significance.

(c)Laboratory assessments

Clinical laboratory tests, including hematology and comprehensive metabolic panel (chemistry), will be performed on recipients as specified in the Schedule of Assessments and Procedures in Table 1. Clinical laboratory tests are to be performed and reviewed by the investigator or qualified designee:Hematology: complete blood count (CBC) with differential will be measured locally for recipients annually.Blood chemistry (Comprehensive Metabolic Panel): A Comprehensive Metabolic Profile must include all of the following measurements: blood urea nitrogen (BUN), creatinine, sodium, potassium, chloride, bicarbonate, glucose, phosphorus, total protein, albumin, creatine kinase (CK), lactate dehydrogenase (LDH), amylase, and liver chemistries including total and direct bilirubin, alanine aminotransferase (ALT), aspartate aminotransferase (AST), and alkaline phosphatase (ALP). The full chemistry panel will be analyzed locally using accepted laboratory methodology at each of the yearly visits.Urinalysis: Instances of proteinuria and/or microscopic hematuria will be recorded.

### Safety monitoring

#### Definition of adverse event (AE)

An AE is any unfavorable and unintended diagnosis, symptom, sign (including an abnormal laboratory finding), syndrome or disease which either occurs during the study, having been absent at baseline, or, if present at baseline, appears to worsen.

#### Definition of serious adverse event (SAE)

An SAE is defined (21CFR 312.32) as any adverse event that results in any of the following outcomes:DeathA life-threatening adverse eventInpatient hospitalization or prolongation of existing hospitalizationPersistent or significant incapacity or substantial disruption of the ability to conduct normal life functionsA congenital anomaly or birth defect

Other important medical events may also be considered an SAE when, based upon appropriate medical judgment, they may jeopardize the patient or subject and may require medical or surgical intervention to prevent one of the outcomes listed above.

### Events of special interest

Clinically significant opportunistic infections (grade 3 Common Terminology Criteria for Adverse Events (CTCAE) or higher or meeting criteria of an SAE), all cancers other than PTLD, and cardiovascular events including revascularization procedures will be reported on dedicated electronic case report forms (eCRFs) for these events of special interest.Active surveillance for myelodysplastic syndrome (MDS)

Myelodysplastic syndromes (MDS) include a group of clonal myeloid neoplasms with presence of cytopenias due to ineffective hematopoiesis, abnormal blood, and marrow cell morphology [9]. These abnormal cells can undergo changes in clonality and progress to acute myeloid leukemia (AML). Some myelodysplastic syndromes have no known cause. Others are caused by exposure to cancer treatments, such as chemotherapy and radiation, or to toxic chemicals, such as tobacco, benzene, and pesticides, or to heavy metals, such as lead.

Active surveillance for MDS consists of full annual physical exam with medical history and evaluation for possible risk factors and CBC with platelets and differential. Additional tests such as vitamin B12 and folate may be required when results of CBC and physical exam are outside of normal parameters which often signal an underlying medical issue. MDS will not be reported as AEs, but as outcomes, and will be collected and reported on dedicated case report forms specifically designed to capture these events.(b)Reporting of pregnancy

Pregnancy is neither an AE nor an SAE, unless a complication relating to the pregnancy occurs. All reports of congenital abnormalities/birth defects are SAEs. Spontaneous miscarriages should also be reported and addressed as SAEs. Elective abortions without complications will not be considered AEs. However, all pregnancies occurring during this study (in subjects or female partners of subjects) are to be reported to the sponsor at the subsequent scheduled visit.

(c)Events to be reported as outcomes rather than adverse events

Rejection episodes, opportunistic infections, BK viremia, cardiovascular events, graft versus host disease (GvHD), post-transplant lymphoproliferative disorder (PTLD), MDS, and new-onset diabetes after transplantation, graft loss, and death are outcomes and will be reported on dedicated case report forms (CRFs) for these events. Causes of death should be reported as SAEs.(iv)Cardiovascular events

Cardiovascular events will include documented acute myocardial infarction, stroke, acute peripheral arterial occlusion, and revascularization procedures. Revascularization procedures will include open and endovascular procedures intended to restore arterial blood flow. Such procedures include bypass, endarterectomy, thrombectomy, angioplasty, stenting, atherectomy, and aneurysm resection/exclusion. Cardiovascular events will be recorded during the study.(e)New-onset diabetes after transplantation (NODAT)

NODAT is defined in this study as the use of an antidiabetic agent/insulin for more than 30 days or any of the following in a subject who was not diabetic at study entry [10]:Fasting glucose 126 mg/dL (7 mmol/L) in more than one occasionRandom glucose 200 mg/dL (11.1 mmol/L) with symptomsTwo-hour glucose after a 75-g oral glucose tolerance test (OGTT) 200 mg/dL (11.1 mmol/L)Hemoglobin A1C (HbA1c) 6.5%.

The development of NODAT will be assessed yearly during the study.(f)Transplant kidney biopsy

Transplant kidney biopsy may be performed for cause at the discretion of a subject’s treating physicians. Biopsies will undergo local pathology review.(g)Estimated glomerular filtration rate (eGFR)

Th eGFR will be calculated yearly during the study using the 4-variable equation from the CKD-EPI 2021 equation, using locally assessed serum creatinine data from the appropriate time points. The calculation will be done by Data Management based on the laboratory and demographic information collected during the course of the study.

CKD-EPI equation:$$\mathrm{eGFRcr}=142\times\min\;(\mathrm{Scr}/\kappa,1)\mathrm\alpha\times\max\;(\mathrm{Scr}/\kappa,1)-1.200\times0.9938\mathrm{Age}\times1.012\;\lbrack\mathrm{if}\;\mathrm{female}\rbrack$$

where:

Scr = serum creatinine in mg/dL.

*κ* = 0.7 (females) or 0.9 (males)

*α* =  − 0.241 (female) or − 0.302 (male)

min (Scr/*κ*, 1) is the minimum of Scr/*κ* or 1.0

max (Scr/*κ*, 1) is the maximum of Scr/*κ* or 1.0

Age (years).

(h)De novo DSA (DnDSA)

Post-kidney transplant testing for dnDSA will be performed using single-antigen bead methodology using a Luminex or similar analytic instrument in a central laboratory. The dnDSA testing may also be performed locally at the time of any “for cause” transplant kidney biopsy per institutional standard of care.(i)Donor chimerism

Mixed chimerism is defined as presence of at least 5% donor cells in either whole blood or in at least one WBC lineage (CD3 + T cells, CD33 + myeloid cells, CD19 + B cells, and/or CD56 + natural killer [NK] cells). The degree of donor chimerism in transplant kidney recipient blood will be assessed centrally using accepted laboratory methodology yearly during the study. Subjects who have lost mixed chimerism (< 5%) do not need to repeat testing at subsequent visits.

### Severity of adverse events

Adverse events, including abnormal clinical laboratory values, will be graded using the National Cancer Institute—Common Terminology Criteria for Adverse Events (NCI-CTCAE) guidelines (Version 5 or higher). Events that are not stipulated in the NCI-CTCAE Version 5 or higher will be assessed according to the criteria below and entered into the eCRF.

It is important to distinguish between serious and severe AEs. An AE of severe intensity may or may not also be considered serious.

### Monitoring and reporting serious adverse events only

All subjects will be monitored closely for SAEs during study participation. Subjects who discontinue prematurely from the study will be encouraged to return for assessment of safety. Follow-up safety information may also be obtained directly from a subject’s physician with source document support whenever applicable (e.g., biopsy results) or from medical records, laboratory reports, and imaging reports.

Whenever possible, symptoms should be grouped as a single syndrome or diagnosis. The investigator should specify the duration (start and end dates) or if the event is ongoing, the severity grade, other medication or therapies have been taken (concomitant medication/non-drug therapy), outcome, and his/her opinion as to whether there is a reasonable possibility that the SAE was caused by the previous study treatment.

In the event of an SAE, the investigator should follow up with the outcome until the clinical recovery is complete and laboratory results have returned to normal or until progression has been stabilized.

The investigator must provide the sponsor appropriate information concerning any findings suggesting significant hazards, contraindications, side effects, or precautions pertinent to the safety of the study treatment. Direct contact information for the Study Medical Monitor will be provided to the institution at time of institutional review.

All SAEs must be reported to the Sponsor within 24 h of the first awareness of the event. The Investigator must complete, sign and date the SAE pages, verify the accuracy of the information recorded on the SAE pages with the corresponding source documents, and send to sponsor:The SAEs will be reported to the sponsor by completing an SAE Report Form. All sections on the form are to be completed. Information that is not available at the time of initial reporting should be submitted as a follow-up. The date of receipt of an initial SAE Report Form will be considered as day 0 for the purpose of determining the time for regulatory reporting of an expedited event and timelines of further study-related activities.The copy of all examinations carried out and the dates on which these examinations were performed will be attached. For laboratory results, the laboratory normal ranges will be included.

It is the Principal Investigator (PI)’s responsibility to notify the IRB of all SAEs that occur at his or her site. The sponsor is responsible for notifying the relevant regulatory authorities of certain safety events, including expedited safety reports. Investigators will also be notified by the Sponsor of all suspected, unexpected, serious, adverse reactions (SUSAR, 7/15 Day Safety Reports) that occur during the clinical trial. Each site is then responsible for notifying its IRB of these additional SAEs.

### Statistics

#### Safety endpoints

Long-term safety will be assessed by summarizing incidence of serious adverse events (SAEs), AEs leading to study withdrawal, and hospitalization rates. Summary statistics will be presented by visit for laboratory data, including hematology, renal function, biochemistry, and vital signs. Adverse events will be classified for seriousness using standard regulatory criteria and for severity according to the National Cancer Institute—Common Terminology Criteria for Adverse Events (NCI-CTCAE) version 5 or higher grading scale whenever feasible.

#### Outcomes of special interest

The number and proportion of subjects with biopsy-proven acute rejection (BPAR), de novo donor-specific antibody (dnDSA) (if applicable), BK viremia, opportunistic infection, post-transplant lymphoproliferative disorder (PTLD), myelodysplastic syndrome (MDS), new-onset diabetes after transplantation (NODAT), graft versus host disease (GvHD), cardiovascular (CV) events, and initiation of immunosuppression will be presented by visit and overall. Transplant kidney loss and subject death will also be summarized by visit and overall.

Outcomes of special interest noted above will not be reported as AEs, but rather as outcomes, and will be collected and reported on dedicated case report forms specifically designed to capture these events; this will include severity and seriousness assessments.

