**Methods/design:**

At the completion of primary follow-up of various Medeor kidney transplant studies, subjects receiving cellular immunotherapy products will be followed annually as per protocolized schedule for up to an additional 84 months (7 years) to evaluate long-term safety. Long-term safety will be assessed by summarizing incidence of serious adverse events, adverse events leading to study withdrawal and hospitalization rates.

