## Background

Thefield of transplantation is actively engaged in studying the induction of effective immune tolerance without the use of immunosuppression. Clinical trials to establish tolerance are using a combination of organ and hematopoietic cell transplantation to achieve immunological tolerance via either full or mixed donor chimerism [1–3]. Full donor chimerism is acquired when the entire recipient hematopoietic system is replaced by donor cells (donor cells > 98%) resulting in deactivation of donor T cells [4]. Mixed chimerism is defined as continued mixing of donor and recipient hematopoietic cells in recipient tissues after transplantation of donor cells. Achievement of mixed chimerism can result in tolerance of organ grafts from the hematopoietic cell donors without the need for immunosuppression [3]. Various centers have employed myeloablative or non-myeloablative conditioning strategies, with total body, local thymic, or lymphoid irradiation, and subsequent donor whole bone marrow transplantation or infusion of granulocyte colony stimulating factor (G-CSF) mobilized CD34 + T cells [5–7]. Establishment of mixed chimerism is associated with lower risk of graft versus host disease (GVHD) and immunodeficiency in comparison to full donor chimerism. The Stanford group reported the long-term outcomes of a pioneering, single-center study in which kidney transplant recipients were given post-transplant conditioning with 10 doses of total lymphoid irradiation (TLI) and 5 doses of anti-thymocyte globulin (ATG) [3]. On completion of TLI, a combination of enriched CD34 + hematopoietic progenitors and a defined number of donor T cells were injected immediately (G-CSF was administered to donors to mobilize progenitors into the blood such that collection was performed via apheresis). Fully HLA-matched patients were given T cells along with the CD34 + cells. The majority of the patients (24/29 fully HLA matched) achieved mixed chimerism for at least 1 year. In the mixed chimerism group, MMF was withdrawn 39 days after cell infusion following kidney transplantation, while calcineurin inhibitors were tapered beginning at approximately 6 months and ceased after approximately 1 year. In the Stanford study, 23/24 (96%) had no evidence of rejection in the first year after withdrawal of immunosuppression. Although two late rejections occurred at 44 and 60 months after rejection, no grafts were lost due to rejection [8]. For this strategy to achieve success, it is imperative to elucidate the long-term safety profile. The monitoring of events such as rejection, graft dysfunction/loss, graft vs host disease (GVHD), and opportunistic infections is important. The MDR-105-SAE study is designed to be a long-term safety monitoring extension trial involving Medeor’s cellular immunotherapy administered to kidney transplant recipients to induce immune tolerance via mixed lymphohematopoietic chimerism. MDR-105-SAE is a Master Protocol that is designed to allow current and future kidney transplant studies to enroll into a single design where safety data can be analyzed in a consistent manner. The initial clinical trial to be enrolled is a phase 3 open label, multicenter, randomized controlled trial to assess safety and efficacy of donor-derived CD34 + hematopoietic stem/progenitor cells and a specified dose of CD3 + T cells administered to recipients of HLA-matched, living donor kidney transplants post total lymphoid irradiation (TLI) and rabbit-anti-thymoglobulin induction, with progressive tapering of maintenance immunosuppression (NCT03363945).

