### Study design

At the time of enrolment in the initial study, the kidney transplant recipients are asked to acknowledge the expectation to participate in a multi-year, long-term follow-up study at the completion of the observation period in the initial study. Upon completion of the initial study, the kidney transplant recipients who received the Medeor product will sign the consent form and begin Study MDR-105-SAE. These patients are expected to participate in the MDR-105-SAE study. Medeor is working with the sites to be able to enroll these subjects into the MDR-105-SAE study upon completion of the initial study. At the completion of primary follow-up of various Medeor kidney transplant studies (called parent studies), subjects receiving Medeor’s cellular immunotherapy products will be followed annually for up to an additional 84 months (7 years) for long-term safety evaluation. No study treatment is involved. All immunosuppression and therapeutic drug monitoring will be managed by treating physicians according to local standard of care (SOC). Any changes in, and reinstitution of immunosuppression drug therapy, will be at the treating physician’s discretion. Post-kidney transplant biopsy will be performed for cause at any time at the discretion of a subject’s treating physician. MDR-105-SAE protocol assessments will be performed annually following study entry. All participants must provide informed consent prior to enrolling into the MDR-105-SAE study.

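### Outcomes of special interest are summarised as plain proportions although follow-up can be incomplete, so an overall proportion of all enrolled subjects would understate 7-year risk for non-fatal outcomes

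*Protocol article*

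**What the plan says.** Under Statistics, Outcomes of special interest, the article names its measure: "The number and proportion of subjects with biopsy-proven acute rejection (BPAR" and similar outcomes such as PTLD, MDS, NODAT, GvHD and cardiovascular events. The list ends with "initiation of immunosuppression will be presented by visit and overall". For graft loss and death, "Transplant kidney loss and subject death will also be summarized by visit and overall". No denominator is given.

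The neighbouring section, Safety endpoints, says: "Long-term safety will be assessed by summarizing incidence of serious adverse events (SAEs), AEs leading to study withdrawal, and hospitalization rates". It does not define the denominator of the incidence or of the rates.

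On length of follow-up, Study design says that subjects "will be followed annually for up to an additional 84 months (7 years) for long-term safety evaluation", which is a maximum without a minimum. The Background describes a master protocol "designed to allow current and future kidney transplant studies to enroll into a single design". Under Discontinuation and withdrawal, "Subjects who withdraw all consent for further participation in the study will be withdrawn from all follow-up assessments"; after that, mortality alone is tracked, from public records. The same section lets the sponsor end the study, or a site, early. Study design times the annual visits from entry into the extension.

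**The concern.** A count divided by subjects estimates a 7-year risk only if each subject is observed until the event, death or 84 months. Here a subject may be lost to every non-fatal outcome after one or two years. If that subject stays in the denominator, the overall proportion treats the unobserved years as event-free.

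The outcomes most exposed are those that can appear late, such as MDS, PTLD, other rejection-related events and graft loss. The extension exists to describe these risks, and the direction of the error is toward apparent safety. The Background also says that data will be monitored continuously, so figures may be read while many subjects have only a few years of follow-up.

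A second issue is the clock. The same visit number means the same time since extension entry. It means the same time since transplant only if the parent studies are equally long.

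**Working it through.** The article gives no event rate, withdrawal rate, entry period or data cut-off, so there is no stated figure to reproduce. Everything below is illustration under assumptions: constant event hazard, loss unrelated to risk, and all enrolled subjects as denominator.

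**Inputs.** Horizon of 7 years (from the document). True 7-year risk R = 20% (assumed). Event hazard h = -ln(1 - 0.20)/7 = 0.0319 per year.

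**1. Complete follow-up.** The crude proportion is 1 - exp(-7h) = 20.0%. There is no understatement.

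**2. Withdrawal.** With annual loss c, let m = -ln(1 - c). The crude proportion is h/(h + m) × [1 - exp(-7(h + m))].

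| Annual loss | m | h/(h + m) | exp(-7(h + m)) | Crude proportion |
|---|---|---|---|---|
| 3% | 0.0305 | 0.511 | 0.646 | 18.1% |
| 5% | 0.0513 | 0.383 | 0.559 | 16.9% |
| 10% | 0.1054 | 0.232 | 0.383 | 14.3% |

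**3. Early data cut, no withdrawal.** With follow-up uniform between a and 7 years, the crude proportion is 1 - [exp(-ah) - exp(-7h)]/[(7 - a)h].

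- a = 3: 1 - (0.9088 - 0.8000)/(4 × 0.03188) = 14.7%.
- a = 1: 1 - (0.9686 - 0.8000)/(6 × 0.03188) = 11.8%.

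**4. A lower risk.** For R = 10%, h = 0.01505. Annual loss of 5% gives 8.4%, 10% gives 7.1%, and follow-up uniform over 1-7 years gives 5.8%. The ratio to the true risk is nearly the same as for R = 20% (0.84 against 0.85 at 5% annual loss).

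**5. Death.** Take R = 10% in the absence of death, 2% annual mortality and otherwise complete follow-up. The crude proportion is 9.3%, and the competing-risk cumulative incidence is also 9.3%. One minus Kaplan-Meier with deaths censored gives 10.0%, which overstates the risk actually experienced. Death therefore does not bias the crude proportion.

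**The case against.** The strongest reply has four parts.

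- **The denominator is unstated and the schedule is the same for all.** Table 1 gives every subject seven annual visits, and no common cut-off is named. If the final analysis waits until the last subject reaches 84 months, rolling entry alone causes no bias. A reader might infer that it does; the document does not support that. Withdrawal still causes understatement, and so does early closure or any earlier cut.
- **By-visit proportions need not be too low.** Among subjects still followed, such a proportion describes that year and shows the time pattern. This stands; what these proportions need is a stated denominator.
- **Misaligned visits are not shown.** A reader might infer that visit columns mix different post-transplant times. That depends on parent-study durations, which the article does not give, and it describes only one parent trial. The most that can be said is that they may not align.
- **An analysis plan may add better estimators.** Proportions are ordinary descriptive output, and leaving time-to-event detail to an analysis plan would be no fault. But the article does name a measure, and that measure, followed literally with all enrolled subjects, understates late risk. The case is for supplementing it, not for removing it.

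**Conclusion.** The point holds in a conditional form. For non-fatal outcomes, an overall proportion of all enrolled subjects lies below the 7-year risk if anyone at risk withdraws, or if data are cut before all subjects reach 84 months. For a true risk of 20%, the assumed scenarios give 18.1% down to 11.8%, a relative shortfall of about 10% (1 - 18.1/20) to 41% (1 - 11.8/20). These sizes rest wholly on the assumed hazard, loss and follow-up spread; the document supports the direction, not the amount.

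One tempting extension should be resisted: that deaths add to the understatement. They do not, because a subject who has died can no longer have the outcome and the crude proportion counts this correctly. Mortality itself is also the outcome least affected by withdrawal of consent, since it remains followed.

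**What to change.** 1. Keep the counts and by-visit proportions, using as denominator the number still followed and at risk, and print that number. Subjects who enter with a failed graft are not at risk of losing that graft, and NODAT applies only to subjects not diabetic at entry.
2. For each outcome add a first-event rate per 100 person-years with an exact (Poisson) 95% confidence interval.
3. Add Aalen-Johansen cumulative incidence with death as competing event, and graft loss as a further competing event for graft-specific outcomes. Do not use Kaplan-Meier with deaths censored for non-fatal outcomes.
4. Present results by parent study, or on time since transplant or cell infusion with delayed entry at extension enrolment.

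The cost is a change of wording and some extra analysis, with two data checks. The dedicated outcome forms must carry onset dates, since the article requires start and end dates only for SAEs. The link to the parent study must supply the transplant or infusion date, which is not among the link fields listed under Baseline characteristics. Limits remain. Outcomes assessed yearly, such as NODAT, may have onset known only to an interval, and neither added estimate corrects for withdrawal that is related to health.
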